### **6.3 Primary endpoint**

The study primary endpoint is the measurement of the endotoxin activity 72 hours after treatment initiation.

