#### **7.5.1 Withdrawal Criteria**

Patients are free to withdraw from the study at any time without having to justify their decision. When a patient decides to withdraw from a study, he/she will be systematically contacted and given the opportunity to provide information about the reason(s) of his/her withdrawal and possible occurrence of an adverse event.

If at any time the investigator considers that malfunctions/AEs could possibly have led to a deficiency in the patient's treatment, the treatment in question shall be discontinued and replaced by a standard treatment.

Patients must be withdrawn from the study if any of the following occurs:

- Any event which, in the opinion of the investigator, may either endanger the health of the patient, or may adversely influence the result of the study;
- Patients refusing or not considered capable, as judged by the investigator, of following instructions of the study;
- In case of clotting of three oXiris™ circuits within 24 hours, or a filter downtime for more than 6 hours, the treatment will be stopped.
- The need for extracorporeal membrane oxygenation (ECMO)
- Patients who die within 72 hours from admission

Withdrawn patients after randomization will be replaced. The reason for withdrawal should be recorded in the Case Report Form (CRF).

If withdrawal is related to the possible occurrence of adverse events, the patient will be followed up according to the adverse event procedure.

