## **7.7 Assignment to study treatment**

#### **Randomization**

All eligible patients will be randomly assign to either conventional SOC treatment according to the Surviving Sepsis Campaign Guidelines (27), or SOC treatment with oXiris™ hemofiltration, or SOC treatment with Toraymyxin™ hemoperfusion within 24 hours of admission to the ICU. Patients will be distributed into these 3 groups, in accordance with the randomization table kept in the investigator's office. The randomization list will be performed using a computer generated (simple random number) scheme.

The allocation sequence is concealed in sealed envelopes held at the study centre, which is available 24 hours a day.

According to paragraph 7.5.1 withdrawn patients will be replaced in order to analyse 10 patients per group.

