### **7.9.3 Visit 3 (24 hours) and Visit 4 (48 hours): Treatment period**

- EAA measurement
- IL-6 and HMGB1
- PCT, Lactate, pH
- SOFA score
- Catecholamine doses: Epinephrine, norepinephrine, dobutamine dose
- Volume requirement
- Hemodynamic parameters: MAP, CVP, HR, CO, ELWI, PVPI
- Ventilation parameters: SaO2, FiO2, SvO2
- Urine output (ml/d)
- AE/SAE
- In the SOC with oXiris™ treatment and SOC with Toraymyxin™ treatment groups:
  - Date and time of initiation and termination of each treatment, anticoagulation usage
  - Documentation of achievement of the treatment period or reason for premature disconnection.
- In the SOC treatment group:
  - If renal replacement therapy has to be performed: type of RRT, type of membrane, treatment conditions, duration, and anticoagulation.

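### oXiris circuit failure is listed as a reason to withdraw and replace the patient, which removes device failures from the analysed oXiris group

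*Protocol*

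**What the plan says.** Protocol section 7.5.1 opens its list with "Patients must be withdrawn from the study if any of the following occurs". One of the five items is the oXiris circuit rule, triggered by "clotting of three oXiris™ circuits within 24 hours, or a filter downtime for more than 6 hours", and that item gives its own consequence: "or a filter downtime for more than 6 hours, the treatment will be stopped". Another item is discretionary and covers any event that, in the investigator's opinion, "may either endanger the health of the patient, or may adversely influence the result of the study".

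After the list the section says "Withdrawn patients after randomization will be replaced". Section 7.7 gives the purpose: "withdrawn patients will be replaced in order to analyse 10 patients per group".

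Section 6.3 defines the outcome: "The study primary endpoint is the measurement of the endotoxin activity 72 hours after treatment initiation". Section 7.8.2.1 takes the EAA sample from an arterial line. Section 7.6.3 plans 48 hours of oXiris, and section 7.6.4 plans two Toraymyxin sessions of 2 hours each. For both device groups, section 7.9.3 records "Documentation of achievement of the treatment period or reason for premature disconnection".

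**The concern.** The rule acts after randomisation, depends on how treatment went, and names one arm. Standard of care has no study device that could fail. A Toraymyxin failure leads to withdrawal only through the discretionary item, so between the two devices the difference is mandatory against discretionary removal.

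If the rule is followed as placed, the ten analysed oXiris patients are those whose circuits did not fail, while the standard-of-care group still contains the same kind of patient. If patients with failed circuits have higher EAA at 72 h than completers, oXiris looks better on the primary endpoint than it is. If they have lower EAA, it looks worse.

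The pilot is meant to supply data for designing later trials (section 13). Those trials will have technical failures too, so the pilot's estimate should include them.

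**Working it through.** **Plan's own figure.** 3 groups × 10 analysed = 30, which agrees with section 13. That total is not disputed; the question is who counts among the ten.

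**Can the endpoint be measured after a stop?** It is timed from the start of treatment, not its completion. The sample comes from an arterial line, not the circuit. Planned oXiris treatment ends at 48 h, so every oXiris patient is off the filter at 72 h. A patient stopped early can be sampled if alive, with an arterial line in place and still participating.

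**Inputs.** Let *f* be the share of oXiris patients who meet this item and no other withdrawal item. Let *d* be the 72 h EAA of failures minus that of completers, in SD units; higher is worse. The protocol gives neither. Assumed: *f* = 5–30%, with the low end allowing for failures withdrawn anyway for death, ECMO or judgement, and *d* = 0.5–1.

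**Shift in the oXiris mean.**
mean(all oXiris) − mean(completers) = *f* × *d*
- Mildest: 0.05 × 0.5 = 0.025 SD
- Largest: 0.30 × 1 = 0.30 SD

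The SE of a 10-versus-10 difference is √(1/10 + 1/10) = 0.447 SD. The ratios are 0.025/0.447 = 0.06 and 0.30/0.447 = 0.67.

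**Against Toraymyxin**, with the same *f* and *d* and a share *g* of its failures removed by judgement, the bias is *d* × *f*(1 − *g*)/(1 − *f g*):
- *g* = 0: 0.025–0.30 SD
- *g* = 0.5: 0.0125/0.975 = 0.013 to 0.15/0.85 = 0.18 SD
- *g* = 1: 0

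**Effect on the test.** Simulation of 200,000 trials per scenario: 10 per arm, normal data with SD 1 within failure-type and other patients, no device effect, failure-type patients absent from oXiris and kept in standard of care. Mann-Whitney test; U ≤ 23 counts as significant in favour of oXiris.

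| *f* | *d* | Favours oXiris | Two-sided |
|---|---|---|---|
| no failures | – | 2.2% | 4.4% |
| 5% | 0.5 | 2.4% | 4.4% |
| 5% | 1 | 2.7% | 4.4% |
| 10% | 0.5 | 2.7% | 4.4% |
| 10% | 1 | 3.3% | 4.7% |
| 20% | 0.5 | 3.4% | 4.7% |
| 20% | 1 | 5.0% | 5.8% |
| 30% | 0.5 | 4.3% | 5.4% |
| 30% | 1 | 7.4% | 7.9% |

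Analysed as randomised, the favourable tail stays at 2.1–2.2%. With the sign reversed (*f* = 20%, *d* = −0.5) it falls to 1.3%. A three-arm Kruskal-Wallis test with *g* = 0 rises from 4.6% to 7.8% in the largest case.

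**How often the rule would bite.** The chance that at least one of the first ten oXiris patients is replaced for this reason is 1 − (1 − *f*)^10. The mean number randomised to analyse ten is 10/(1 − *f*).

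| *f* | At least one replaced | Randomised for 10 analysed |
|---|---|---|
| 5% | 40% | 10.5 |
| 10% | 65% | 11.1 |
| 20% | 89% | 12.5 |
| 30% | 97% | 14.3 |

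**Timing.** From the planned start (01.08.2013) to version 1.7 (16.06.2016) is 1,050 days; to the planned end (01.02.2017) it is 1,280 days. 1,050/1,280 = 82%. At even accrual, 30 × 18% = 5.4 patients remain.

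**The case against.** The strongest reply is that this is only a misplaced line. It is the one item in the list that names its own consequence, and that consequence is a treatment stop. Just before the list, section 7.5.1 says that when a malfunction or adverse event may have led to deficient treatment, the treatment is discontinued and replaced by a standard one, with no mention of leaving the study. Section 12.3 keeps patients whose clinician chose an alternative treatment in follow-up and analysis. On that reading no bias arises.

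The ambiguity is real, but it does not settle the matter. Because the section already has a separate treatment-stop paragraph, placing this item under the withdrawal heading reads as a different instruction. Two centres could apply it differently. The malfunction paragraph also sharpens the contrast: a failed Toraymyxin column can be stopped under it and the patient kept, while an oXiris failure falls under a mandatory heading. Section 12.3 supports retention only by analogy, since a clotted circuit is not a clinician's choice of alternative treatment.

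Two further points stand. The size rests wholly on assumptions: the trigger is demanding, the circuit is heparinised except at high bleeding risk, and the sign of the difference is unknown. And in the mild scenarios the tests barely move; two-sided rejection stays below 5% in five of eight.

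It can also be said that a mechanistic pilot may prefer patients who received the device, and that analysis sets belong in an SAP. A completed-treatment analysis is legitimate as a secondary one applied to both devices, but no SAP can restore 72 h samples that were never taken because the patient was withdrawn. A device-specific bedside stop is itself reasonable for 48 hours of continuous treatment.

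**Conclusion.** The concern holds as a reading of the text as placed, with medium confidence. Tying a bedside stop to leaving the study creates a post-randomisation exclusion that is mandatory in one arm, impossible in another and discretionary in the third, and the primary endpoint does not require it.

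For oXiris against standard of care the possible bias spans the 0.025–0.30 SD range. Against Toraymyxin it runs from that same range down to zero, depending on how many Toraymyxin failures are also removed. These figures depend on the assumed failure share and EAA difference, and the direction favours oXiris only if failures do worse. The protocol does not show which case applies. It should be fixed because the change is cheap and protects the primary comparison, not because a large bias has been shown.

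**What to change.** Keep the stopping rule but move it out of the withdrawal list. State that stopped patients:
- keep the T24–T72 and day 28 assessments;
- are analysed in the oXiris group as randomised;
- are not replaced for this reason.

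Handle stopped or failed Toraymyxin sessions in the same way. Report device failure and early disconnection by arm. Make any completed-treatment analysis secondary and apply it to both device arms.

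If any patients have already been withdrawn under this item, list them by arm with the reason and last EAA, include any 72 h EAA recorded, and show the primary result with and without their replacements.

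**Cost.** Amendment wording. Treatment times and reasons for disconnection are already recorded; the number of clotted circuits and the downtime may need a CRF field. On the assumed range, 0.5 to 4.3 fewer oXiris patients need to be randomised (10.5 − 10 to 14.3 − 10). The bedside safety rule does not change.

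**Downsides.** The reported oXiris effect may be smaller. With about 82% of the planned study period gone at version 1.7, patients withdrawn earlier may lack 72 h data, which new wording cannot restore.

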### **6.4 Secondary endpoints**

The secondary endpoints are the following:

- Measurement of IL-6 and HMGB1 T0 i.e. patient inclusion, at T24 hours, T48 hours, and T 72 hours after treatment initiation;
- Routine measurements of norepinephrine dose, inotropic score, and vasopressor dependency index T0, T24, T48 and T72;
- Haemodynamics: MAP, CVP, HR, CO, ELWI, PVPI T0, T24, T48 and T72
- Routine measurements of volume requirement T0, T24, T48 and T72;
- Routine measurements of ventilation parameters PO2/FiO2, SvO2 T0, T24, T48 and T72;
- Urine output (ml/d)
- Lactate, procalcitonin and pH measurements at T0, T24, T48 and T72 after treatment initiation;
- SOFA score calculation at T0, T24, T48 and T72 ;
- Incidence of renal failure, ICU length of stay
- Patient survival at D28;
- Recording of AEs/SAEs

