After the subject has entered the study the clinician remains free to give alternative treatment to that specified in the CIP at any stage if he/she feels it is in the subject's best interest, but the reasons for doing so should be recorded. In these cases, the subject remains within the study for the purposes of follow-up and data analysis. All subjects are free to withdraw at any time from the CIP treatment without giving reasons and without prejudicing further treatment.

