## **13 Statistical considerations**

As mentioned, the endotoxin activity is not well described in the literature, which makes a sample calculation difficult. Therefore, this trial was designed as a pilot study analysing 30 patients in order to collect data enabling an accurate design of future investigations. Dependent and independent continuous variables will be compared using Wilcoxon and Mann-Whitney, respectively. In cases of serial measures repeated measures statistics will be applied. For multiple comparisons overall tests will be used: ANOVA for continuous variables and Kruskal-Wallis tests for ordinal scaled variables. Categorical data will be compared using Fisher's exact and  $\chi^2$  test. The normal distribution of study variables will be confirmed using Kolmogorov-Smirnov test. A P value < 0.05 will be considered statistically significant. To obtain adjusted differences in outcomes for the two study populations, logistic regression will be performed to control for factors or confounders that are significantly different ( $p < 0.05$ ) between compared groups. Data will be analysed using the Statistical Package for Social Sciences (SPSS Windows, version 19.0; SPSS Inc., Chicago, IL).

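### Randomised patients who die within 72 hours of admission, or whom the unblinded investigator withdraws, are replaced, so the analysed groups are selected on post-randomisation events and D28 survival loses its early deaths

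*Protocol*

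**What the plan says.** Section 7.5.1 (Withdrawal Criteria) lists events that make withdrawal from the study mandatory. They include "Patients who die within 72 hours from admission", need for ECMO, and any event that in the investigator's opinion may endanger the patient or "may adversely influence the result of the study". Another bullet begins "In case of clotting of three oXiris™ circuits within 24 hours", adds filter downtime of more than 6 hours, and ends by saying that treatment is stopped.

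The section then states: "Withdrawn patients after randomization will be replaced". Section 7.7 gives the purpose: "withdrawn patients will be replaced in order to analyse 10 patients per group". Section 13 matches this: "this trial was designed as a pilot study analysing 30 patients".

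The primary endpoint (6.3) is EAA 72 hours after treatment initiation. Secondary endpoints (6.4) include SOFA at T0, T24, T48 and T72, and "Patient survival at D28". Section 7 describes the trial as open. Section 7.7 places randomisation within 24 hours of ICU admission. Section 12.3 says that when a clinician gives treatment other than that planned, "the subject remains within the study for the purposes of follow-up and data analysis".

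**The concern.** Randomisation makes the three groups comparable at the moment of allocation. A rule that removes patients for what happens afterwards, and enrols others in their place, gives that up.

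The death rule is the plainest case. A death in the first 72 hours is an event of the 28-day survival endpoint, and the rule takes it out and substitutes another patient. If a device altered early mortality in either direction, that part of the effect would be reduced or lost in the survival comparison.

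The investigator-opinion criterion adds discretion. A person who knows the allocation is told to withdraw patients whose course may affect the result unfavourably.

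Section 13 says the pilot exists to supply data for the accurate design of later trials. Mortality and attrition are among the figures such a design needs, and the rule distorts them. Because the protocol itself fixes who is replaced and who is analysed, this is not a detail left to a statistical analysis plan.

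**Working it through.** **The plan's own figure.** 3 groups × 10 analysed = 30, which agrees with section 13. It is a count after replacement. The protocol gives no power, event rate or standard deviation.

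**Inputs not in the protocol (assumptions).** m = mortality at day 28 among all randomised, taken as 30% to 50% with 40% as the central value. e = share of randomised patients who die within the 72-hour window, taken as 5% to 25%.

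**Analysed mortality.** With early deaths removed it is (m − e)/(1 − e).
- m = 40%, e = 10%: (0.40 − 0.10)/0.90 = 33.3%
- m = 40%, e = 25%: (0.40 − 0.25)/0.75 = 20.0%

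| e | m = 30% | m = 40% | m = 50% |
|---|---|---|---|
| 5% | 26.3% | 36.8% | 47.4% |
| 10% | 22.2% | 33.3% | 44.4% |
| 15% | 17.6% | 29.4% | 41.2% |
| 20% | 12.5% | 25.0% | 37.5% |
| 25% | 6.7% | 20.0% | 33.3% |

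**Number to randomise.** 30/(1 − e): 30/0.90 = 33.3 and 30/0.75 = 40. The expected number of deaths removed is e × 30/(1 − e): 3.3 and 10.

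**Would the rule be used?** P(at least one early death among 30) = 1 − (1 − e)^30, which is 78.5% at e = 5% and 95.8% at e = 10%.

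**Effect on a comparison (illustrations with chosen rates).**
- Early deaths 15% vs 25%, later deaths 25% of all randomised in both arms. True mortality is 40% vs 50%, a difference of 10 points. Analysed: 0.25/0.85 = 29.4% vs 0.25/0.75 = 33.3%, a difference of 3.9 points.
- Early deaths 20% vs 10%, and 25% of 72-hour survivors dying later in both arms. True survival is 0.80 × 0.75 = 60.0% vs 0.90 × 0.75 = 67.5%. Analysed survival is 75.0% in both, so the 7.5-point difference disappears.

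**EAA and SOFA.** A patient who dies before T72 has no T72 value under any rule. What the rule adds is the loss of that patient's earlier readings and replacement by someone who survived the window. A simulation with no device effect assumed an EAA standard deviation of 0.15 and a correlation of 0.3 to 0.7 between severity and EAA. Removing the sickest 10% in one arm and 30% in another gave a false difference of 0.014 to 0.032 units, about 0.1 to 0.2 SD. Removing 10% in both arms gave essentially no difference between arms but lowered both means. The direction was built in by assuming that sicker patients have higher EAA, so this shows only that a bias can arise.

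**The clocks.** The death window runs from admission. T72 runs from treatment start. If treatment starts s hours after ICU admission, T72 falls at 72 + s hours. With s up to 24 (treatment starting at randomisation), deaths between 72 and up to 96 hours after admission are outside the withdrawal rule yet have no primary value.

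**7.5.1 against 12.3.** The clotting and downtime bullet stands in a list headed by withdrawal from the study, but its own ending speaks only of treatment. If it means withdrawal, it removes failed deliveries from the oXiris arm alone, since no matching Toraymyxin criterion is listed. It would then also conflict in part with 12.3, which keeps patients on alternative treatment in follow-up and analysis.

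**The case against.** The strongest reply is that this is a small pilot with a mechanistic primary endpoint and no power claim, and that replacing patients who cannot supply that endpoint is a practical way to obtain 10 values per arm. At 10 per arm, mortality of 40% vs 50% is a difference of one patient, with a 95% half-width of about 1.96 × √(0.4 × 0.6/10 + 0.5 × 0.5/10) = 43 points. Shrinking it to 3.9 points would change no conclusion on survival. That stands as to inference. It does not answer the distorted mortality and attrition figures carried into a later trial.

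Several stronger readings are tempting and are not supported:
- **That early deaths vanish from the record.** They do not. Withdrawal reasons go in the CRF (7.5.1), adverse events are collected to day 28 or death (8.2), and an event leading to death is an SAE (8.1). Early mortality by arm could be recovered. The fault lies in the analysed groups and D28 survival, not in safety recording.
- **That failed oXiris deliveries are certainly dropped from one arm.** The bullet's ending allows a treatment-only meaning. It is ambiguous and needs reconciling.
- **That EAA and SOFA at T72 are biased in a known direction.** The document supports no direction or size.
- **That 12.3 flatly contradicts 7.5.1.** It concerns a clinician's choice of other treatment. It does not address death or ECMO, so the conflict is partial.
- **That the criterion on following instructions removes most of this population.** Section 12.3 concerns capacity to consent and provides for enrolling patients without it. That is a different matter.
- **That only replacements are analysed.** The ten per group are the patients not withdrawn plus any replacements.

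**Conclusion.** The point holds for the analysed groups in general and most directly for 28-day survival. As written, the protocol withdraws and replaces patients for early death, ECMO and unblinded investigator judgement, so the groups analysed are selected on events after randomisation.

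On assumed rates of 40% mortality at day 28 and 10% to 25% early death, analysed mortality reads 33% down to 20%, with about 33 to 40 patients randomised for 30 analysed. These sizes rest wholly on the assumed rates, and the table in the working shows how they move. The structure of the error does not depend on them: any early death in a randomised patient is removed from a survival endpoint to which it belongs.

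For EAA and SOFA, the loss of earlier readings and the replacement by survivors are real, but the bias cannot be sized. The oXiris bullet and the mismatched 72-hour clocks are wording faults to settle in the same amendment.

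**What to change.** In sections 7.5.1 and 7.7:
1. Separate stopping study treatment from leaving the study. Reconcile the oXiris bullet with section 12.3, leaving every clinical stopping rule as it is.
2. Remove death within 72 hours, and possible influence on the study result, as reasons to leave the analysis.
3. Analyse all randomised patients in their assigned arm and count every death in 28-day survival. The one exception is patients whose data must be destroyed on refusal under 12.3; report their number by arm. Without this exception the rule could not be followed, because consent is often sought after randomisation.
4. Use all EAA and SOFA readings up to death and report deaths before T72 by arm, counted from treatment start. A sensitivity analysis that ranks death before T72 as worst is optional, since it turns a mechanistic endpoint into a composite.
5. If enrolment continues until each arm has 10 observed T72 values, drop nobody already randomised. Present the evaluable set as a labelled supplementary analysis.

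The cost is an amendment and a little more analysis. The trial ends with either fewer than 10 T72 values in some arms or slightly more than 30 randomised, which the present replacement rule already implies. Version 1.7 is dated 16.06.2016 and last patient out is planned for 01/02/2017, so new wording cannot recover readings never taken on patients already withdrawn. Deaths already recorded can still be counted.

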| Number of Subjects: | 30 patients in total                                                                                                                                                                                                                                                                                                                                                                                                                                                                                                                                                                                                                                                                                                                                                                                                                                                                                                                                                                                                                                                                                                                                                                                                                                                                                                                                                                                                                                                                                                                                                                                                                                |

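### Randomised patients who die within 72 hours of admission are withdrawn and replaced, so the D28 survival comparison is made in a set selected on survival itself

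*Protocol*

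**What the plan says.** Protocol section 7.5.1 opens its list with "Patients must be withdrawn from the study if any of the following occurs". One entry is "Patients who die within 72 hours from admission"; another is a need for ECMO. The section then states "Withdrawn patients after randomization will be replaced". Section 7.7 (Randomization) says why: "withdrawn patients will be replaced in order to analyse 10 patients per group". The synopsis gives "30 patients in total", and the synopsis and section 13 both speak of analysing 30 patients.

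Section 6.4 lists "Patient survival at D28" as a secondary endpoint. Section 6.3 defines the primary endpoint as "the measurement of the endotoxin activity 72 hours after treatment initiation". Section 7.7 allows randomisation up to 24 hours after ICU admission.

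The last paragraph of section 12.3 keeps patients who receive treatment other than that specified in the study for follow-up and data analysis. No section does the same for patients who die early.

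**The concern.** Death within 72 hours is an outcome that occurs after randomisation, and it counts towards D28 survival. A rule that takes these patients out and fills their places lets the outcome decide who is analysed. Each replacement enters the analysed set only by living past the same window, although that patient may still die before day 28.

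If early mortality differs between arms, the analysed D28 comparison no longer estimates the difference between the randomised groups. An excess or a saving of early deaths drops out of it, and an arm with more early deaths can look equal or better. The EAA, cytokine, vasopressor and SOFA values already collected up to T48 in patients who die early are lost to the comparison as well. For a pilot meant to supply planning data for later trials (section 13), survival in all randomised patients is a figure the next design would need.

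The time windows also differ. The criterion counts from admission, whereas T72 counts from treatment initiation, so some deaths before T72 fall outside it.

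**Working it through.** **Inputs from the protocol.** Three groups, 10 analysed per group (7.7); 30 analysed in total (synopsis, 13); randomisation within 24 h of ICU admission (7.7); primary measurement at 72 h from treatment initiation (6.3). The plan's own figure reproduces: 3 × 10 = 30.

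**Assumed inputs.** The protocol states no mortality rate. Let e be the probability of death within 72 h of admission and M the D28 mortality in all randomised patients. The values below are illustrations.

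**1. D28 mortality in the analysed set.** Early deaths leave both numerator and denominator, so analysed mortality = (M − e) / (1 − e).

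| Assumed M and e, arm A | Assumed M and e, arm B | Analysed A | Analysed B |
|---|---|---|---|
| 40%, 10% | 40%, 25% | 0.30/0.90 = 33.3% | 0.15/0.75 = 20.0% |
| 50%, 30% | 35%, 10% | 0.20/0.70 = 28.6% | 0.25/0.90 = 27.8% |
| 40%, 20% | 55%, 40% | 0.20/0.80 = 25% | 0.15/0.60 = 25% |

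Row 1: no true difference reads as a 13-point advantage for the arm with more early deaths. Row 2: a 15-point excess reads as less than 1 point. Row 3: a 15-point excess reads as zero, because mortality after 72 h is the same in both arms.

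**2. How often the rule would act.** P(at least one early death among the first 30) = 1 − (1 − e)^30, which is 1 − 0.90^30 = 96% at e = 10%.

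**3. Number randomised.** To analyse 30, about 30/(1 − e) must be randomised: 30/0.95 = 31.6, so 32, at e = 5%; 30/0.70 = 42.9, so 43, at e = 30%.

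**4. The time windows.** Reading admission as ICU admission, and taking treatment to start at randomisation (section 7.9.2 places both at Visit 2), T72 can fall as late as 24 + 72 = 96 h after admission. A death between 72 h and 96 h is then not covered by this criterion, yet there is no T72 value. Section 7.5.1 does not say whether hospital or ICU admission is meant.

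**The case against.** Several stronger readings are tempting, and the documents do not support them.

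- **A reader might infer that the rule biases every 72-hour endpoint.** T72 EAA cannot be measured in a patient who has died, whatever the withdrawal rule. Survivor-only T72 means have the same expectation with or without replacement. That is truncation by death and is not caused by this rule. Deaths in the gap before T72 would likewise lack a value after the fix.
- **A reader might infer that early deaths or attrition are hidden.** The reason for withdrawal goes into the CRF (7.5.1), adverse events are collected to day 28 or death (8.2, 8.3), the date of death is recorded (7.9.5), and the monitor checks the numbers withdrawn (14.1). Early deaths by arm can be recovered.
- **A reader might infer that the total of 30 is wrong.** It agrees with the stated number analysed.
- **A reader might infer that the rule fails its own target of 10.** Section 7.7 promises 10 analysed patients, not 10 T72 values, and the first withdrawal bullet is broad enough that it might take in some gap deaths.

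The sponsor can add that this is a declared pilot without a power claim. With 10 per arm, the 13-point artefact in row 1 is about 1.3 patients, against a 95% interval of roughly ±38 points: 1.96 × √(0.333 × 0.667/10 + 0.20 × 0.80/10) = 0.38.

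These points narrow the concern but do not remove it. Wide intervals do not justify a biased estimate when the unbiased one uses data already collected. Nor is this a detail left to an analysis plan: the protocol itself fixes withdrawal, replacement and the number analysed. If the dead stayed in the analysis, replacing them would give more than the 10 per group that section 7.7 states.

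**Conclusion.** The point stands for D28 survival and for the T0 to T48 data of patients who die early. By written rule, the D28 comparison is made in patients selected for having survived the first 72 hours, and no section restores the others.

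The size depends on early mortality, which the protocol does not give. Under the assumed rates the distortion is 13 to 15 percentage points and can run in either direction. If early mortality were equal across arms, analysed mortality would still be too low in each arm. If it were nil, the rule would have no effect. At an assumed 10% the rule would almost surely operate at least once.

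The mismatch between the admission clock and the treatment clock is a smaller matter of wording. The ECMO entry raises a separate inconsistency: 7.5.1 withdraws and replaces these patients, while 12.3 keeps patients given alternative treatment in follow-up and analysis.

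**What to change.** 1. State in 7.5.1 and 7.7 that death does not remove a randomised patient from the analysis.
2. Analyse D28 survival in all randomised patients by assigned arm.
3. Report deaths before T72 by arm, counted from randomisation.
4. Keep the T0 to T48 values of patients who die, and add a sensitivity analysis of T72 EAA that ranks death before T72 as worst.
5. If 10 T72 values per arm are wanted, allow extra patients to be randomised, provided those who died stay in the analysis. Report the number randomised next to the 30 analysed.
6. Separate stopping of study treatment from removal from analysis in 7.5.1, and reconcile 7.5.1 with 12.3 for patients who need ECMO. No clinical rule needs to change for this.

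For deaths, the cost is amendment wording and a slightly different analysis, with no new data. For ECMO patients, any added follow-up depends on how the two sections are reconciled.

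If no extra patients are randomised, an assumed 20% early death leaves about 8 rather than 10 T72 values per arm. A two-arm confidence interval is then about 14% wider: √(10/8) × t(14 df)/t(18 df) = 1.118 × 2.145/2.101 = 1.14. Extra randomisation under item 5 avoids this.
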